## Abstract

Background: Physical inactivity is a serious public health problem for people of all ages and is currently the fourth highest global risk factor for mortality. The transition period from adolescence to adulthood coincides with a marked reduction in participation in physical activity, with more than 50% (and up to 80%) of young adults stopping physical activity. This decrease in physical activity is more evident in women than in men. Despite efforts, existing programs face challenges in effectively initiating and maintaining physical activity among individuals, particularly women, for extended durations. To address these limitations, the Women’s Involvement in Steady Exercise (WISE) randomized controlled trial (RCT) seeks to assess the efficacy of a digital high-intensity training intervention complemented by nutritional plans and other health-related advice. Methods: The study will be a three-center, randomized (1:1), controlled, parallel-group trial with a six-month intervention period. A total of 300 participants will be recruited at three study sites in Spain, Serbia and Italy. The participants will be randomized to one of the two groups and will follow a six-month program. The primary outcome of the study is the daily step count. Self-reported physical activity, the adherence to the exercise program, body composition, physical activity enjoyment, quality of sleep and physical capacities will also be evaluated.

## 1. Introduction

Physical inactivity is a serious public health problem for people of all ages and is currently the fourth highest global risk factor for mortality [1]. A lack of physical activity is related to pathologies such as type 2 diabetes, coronary heart disease and certain types of cancer, among others [2]. In addition, in the case of children and adolescents, several studies have shown that those who perform greater physical activity have better physical and mental health and better psychosocial well-being than those who lead a sedentary lifestyle [3].

It is estimated that 23% of the adult population and 81% of adolescents (between 11–17 years) do not meet the physical activity recommendations of the World Health Organization (WHO) [4]. These indications suggest that children and adolescents between 5 and 17 should perform at least 60 min a day of moderate-to-vigorous-intensity exercise, mostly aerobic, as well as incorporating strength/impact activities at least three days a week. On the other hand, the recommendations for adults between the ages of 18 and 64 are that they should perform at least 150–300 min of moderate-intensity aerobic physical activity, or at least 75–150 min of vigorous-intensity aerobic physical activity, combined with muscle-strengthening activities at moderate intensity or greater on two or more days a week [5].

Statistics from the European Union (EU) member states reveal that 60% of individuals aged 15 and above rarely or never participate in exercise or sports, and over 50% seldom or never engage in other forms of physical activity such as cycling, walking, gardening or household chores [6]. The transition period from adolescence to adulthood coincides with a marked reduction in participation in physical activity, with more than 50% (and up to 80%) of young adults stopping physical activity [7]. This decrease in physical activity is more evident in women than in men. According to the data provided in 2020 by the Survey of Sports Habits in Spain, in annual terms, only 53.9% of women practiced sport in 2020 compared to 65.5% of men. The difference between men and women is most evident in younger age groups: 15% of men aged 15–24 never exercise or play sports compared to 33% of women in the same age range [8].

Evidence reports that the best way to combat the consequences of a sedentary lifestyle is to exercise. However, one of the great problems of sports practice is the lack of adherence [9], that is, the lack of continuity to perform some type of physical activity. Barriers to physical activity and sports participation for women include a lack of time, lack of interest or low motivational level, societal norms and expectations related to gender roles and appearance, lack of social support, fear of injury, limited access to exercise facilities or prohibitive costs of training programs, cultural norms and stereotypes and personal beliefs and attitudes, among other factors. These barriers may vary by age, ethnicity and socio-economic status [10,11,12,13,14].

In order to overcome these barriers, different strategies have been described, such as group training, supervised training and different, more “dynamic” exercise modalities such as those that combine moderate aerobic exercise with strength exercise or high-intensity functional training [15]. One of these interventions is High Intensity Interval Training (hereinafter HIIT). This training modality is acquiring great acceptance as one of its main advantages is that it is a form of exercise of short duration (the sessions usually last between 20 and 30 min). However, despite its short execution time, its effects are maintained in the long term (up to 48 h after having completed the training [16]). Furthermore, it has been seen in some studies that participants prefer this type of exercise to a traditional exercise program because they enjoy it more and find it more motivating [17]. A review of HIIT programs has shown that a range of HIIT protocols, including those that use cycling, running and bodyweight exercises, can enhance cardiorespiratory fitness and other health markers in both healthy individuals and those with chronic diseases such as diabetes and hypertension [18]. Other studies have suggested that HIIT programs involving Tabata-style intervals (i.e., exercise periods that involve performing an exercise at maximum intensity for 20 s, followed by 10 s of rest, and repeating this cycle for a total of four minutes) can be effective for improving fitness in inexperienced populations [19,20]. However, it is worth noting that a gradual progression and individualized programming are crucial to prevent injury and ensure long-term success with a HIIT program.

The evidence also reports that new technologies could be a great tool to combat the aforementioned adhesion problems. Some studies have shown that new technologies, such as phone apps or smartwatches, can be a useful support to improve exercise adherence [21,22]. The Xiaomi Mi Band smartwatches have shown good accuracy in the measurement of steps [23,24], although more studies are needed in this regard as there is a lack of literature on the subject. Leveraging behavior change theories and techniques (BCTs) is a critical factor in enhancing the effectiveness of e-health interventions as they enable the targeting of key components for behavior change [25]. The Consolidated Standards of Reporting Trials (CONSORT) statement [26] and the World Health Organization (WHO) [27] have stressed the importance of incorporating a theory-based approach in the creation of digital interventions, according to their recommendations.

On the other hand, nutrition is well-recognized as a central component of a healthy lifestyle. Maintaining a healthy diet is a challenge for adolescents and young adults [28]. Dietary behaviors also tend to worsen during early adulthood, when young individuals transition into independent living [29]. Dietary behavior change programs are needed that appeal to large numbers and diverse types of people who could benefit from the educational/behavior change procedures. Innovative approaches to dietary change are needed to engage participants in enjoyable experiences to reach the largest number of participants.

For these reasons, in order to engage young women in physical activity habits, it is necessary to create a new perspective of promoting exercise. New ways of encouraging physical activity should be included. These should include a combination of new technologies with shorter and more varied exercise sessions that facilitate women’s enjoyment of physical activity and appear as a new way of improving their adherence to exercise within a healthier lifestyle.

### Study Aims

The primary goal of the Women’s Involvement in Steady Exercise (WISE) randomized controlled trial (RCT) is to evaluate the adherence to a six-month HIIT program, accompanied by nutritional plans and other health-related advice, delivered via a mobile application, among sedentary young women aged 15 to 24 years. This trial aims to determine the effectiveness of the exercise intervention by assessing the changes in the participants’ daily step count over the six-month period. The secondary objectives include analyzing the medium- and long-term effects of the program on various variables, including physical activity, anthropometric measurements, body composition, physical capacities, well-being and psychological mediators.

## 2. Materials and Methods

### 2.1. Study Design

The WISE experimental RCT consists of three components embedded into a smartphone app: (1) a remote HIIT program with video sessions; (2) an interface that includes health information; (3) an activity monitoring tool. The study will be a three-center, randomized (1:1), controlled, parallel-group trial with a six-month intervention period. Young women will be recruited from the communities at three study sites in Spain (University of Valencia, Valencia), Serbia (University Nikola Tesla, Belgrade) and Italy (SPORTLAB, Parma). This study protocol will be reported in accordance with the Standard Protocol Items: Recommendations for Interventional Trials (SPIRIT) guidelines [30], and will follow the CONSORT (Consolidated Standards for Reporting Trials) guidelines for the transparent reporting of parallel group randomized trials [31]. To gain a comprehensive understanding of the study design, refer to Figure 1.

### 2.2. Participants

#### 2.2.1. Eligibility Criteria

Participants eligible for the trial must comply with all of the following:

1.Young women aged between 15 and 24 years.2.Sedentary young women who do not comply with the WHO recommendations for physical exercise and with a low international physical activity questionnaire (IPAQ) score, which means that they do not perform at least one of these:
Three or more days of vigorous activity for at least 20 min a day.Five or more days of moderate-intensity activity.Walk at least 30 min a day every day.Five or more days of combining activities of moderate or vigorous intensity or walking reached a minimum of 600 MET (min/week).

The presence of one of the following criteria will lead to the exclusion of the participant:1.Young women with diabetes.2.Young women with possible heart problems or another type of contraindication that does not allow physical exercise (for this item the physical activity readiness questionnaire (PAR-Q) survey is used).3.Young women who are not willing to wear the smartwatch during the six-month intervention.4.Young women who have contracted severe COVID-19 prior to the intervention. Severe COVID-19 is defined as dyspnea, a respiratory rate of 30 or more breaths per minute, a blood oxygen saturation of 93% or less, a ratio of the partial pressure of arterial oxygen to the fraction of inspired oxygen (Pao2:Fio2) of less than 300 mm Hg, or infiltrates in more than 50% of the lung field [32].

#### 2.2.2. Recruitment

A total of 300 participants (150 per group) will be recruited between the three countries. Each country will recruit 100 young women for the study. Dissemination of the project will be conducted via email and posters in close contact with universities, schools and local authorities. Through the information of the posters and emails, interested participants will contact the investigators and will be informed about the study in order to decide if they finally want to participate. Those willing to participate will be summoned for a personal interview to check if they meet the inclusion criteria. Participants who meet the inclusion criteria will be invited to participate in the study and will sign a written consent form before being included in the study. At the start of the study, a wearable device (Xiaomi Mi Band 5) will be distributed to all participants.

#### 2.2.3. Sample Size and Power Analysis

Sample size estimations were derived from the primary outcome measure of daily step count, measured using the Xiaomi Mi Band 5. A priori sample size calculation was conducted based on a previous meta-analysis [33], which reported an effect size of d = 0.51 (95% CI 0.12 to 0.91, I² = 90%), compared with control groups, for physical activity interventions that included wearables and smartphone apps. Our sample size estimation was based on an intermediate effect size of d = 0.50.

To detect a difference equivalent to an effect size of 0.5 on the primary outcome with 90% power and a two-sided type I error of 0.05, a sample size of 240 is required. Specifically, assuming that the statistical unit is an individual day and considering an intraclass correlation coefficient of 0.5 to account for interindividual and intraindividual variability, a total of 2002 individual days per group (equivalent to 22 participants per group) are necessary. We suggest including a total of 300 participants (150 per group) in order to protect against a potential dropout of 20%, inherent to such a trial.

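### The sample-size paragraph gives two incompatible requirements (240 in total and 22 per group), and neither follows from d = 0.5 at 90% power; the planned 300 is nevertheless conservative

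*Protocol article*

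**What the plan says.** Section 2.2.3 (Sample Size and Power Analysis) sizes the trial on daily step count and fixes the effect: "Our sample size estimation was based on an intermediate effect size of d = 0.50". For that effect it states that "with 90% power and a two-sided type I error of 0.05, a sample size of 240 is required".

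The next sentence is offered as the detail behind this number. It changes the unit, "assuming that the statistical unit is an individual day and considering an intraclass correlation coefficient of 0.5", and concludes that "a total of 2002 individual days per group (equivalent to 22 participants per group) are necessary".

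The paragraph ends with an enrolment of 300 (150 per group) to allow for 20% dropout. Section 2.2.2 (Recruitment) gives the same 300, and section 2.1 gives 1:1 allocation in parallel groups.

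**The concern.** The second sentence should explain the first, but 22 per group is 44 women and the first figure is 240. The two differ by a factor of 240/44 = 5.5 for the same effect, power and significance level. The 240 must count participants, because 240/0.8 = 300 is the enrolment.

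The stated 90% power belongs to neither figure: it is too low for 240 and too high for 22 per group. What is at stake is the justification, since recruitment follows the 240. Even so, a published statement that 22 per group is what 90% power requires could later be cited to call the trial adequately powered after heavy attrition. The Conclusions section itself names adherence, including wearing the watch, as a challenge.

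**Working it through.** **Inputs from the protocol article.** d = 0.5, power 90%, two-sided alpha 0.05, ICC 0.5, 2002 days and 22 participants per group, 240 required, 300 enrolled, dropout 20% (all section 2.2.3); 1:1 allocation (section 2.1).

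**Input inferred.** Days per woman: 2002/22 = 91. The article does not state this number.

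**1. Dropout step.** 240/(1 − 0.20) = 300. This reproduces, so 240 means 120 evaluable per group.

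**2. Requirement with the participant as unit.**
- n per group = 2(z₀.₉₇₅ + z₀.₉₀)²/d² = 2(1.960 + 1.2816)²/0.25 = 84.06.
- The t-test solution is 85.03, so 86 per group, 172 in total. The stated 240 does not reproduce.

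Other readings, total sample size by the normal formula:

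| Variant | Total |
|---|---|
| One-sided 0.05 | 138 |
| 80% power | 126 |
| 95% power | 208 |
| d = 0.51 | 162 |
| Two-sided alpha 0.025 | 200 |
| Two-sided alpha 0.01 | 240 |

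Of these, only alpha 0.01 gives 240, and it contradicts the stated 0.05.

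**3. What 120 per group provides (t-test).** Power at d = 0.5 is 97.1%. The effect detectable with 90% power is d = 0.42.

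**4. What 22 per group provides, participant as unit.** Power at d = 0.5 is 36.7% by t-test (38.1% by normal approximation).

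**5. What 22 per group provides, day as unit.** This assumes that d = 0.5 is scaled on the day-level standard deviation, which the article does not say.
- Design effect = 1 + (91 − 1) × 0.5 = 46.
- Effective observations per group = 2002/46 = 43.5, against 84.06 needed.
- Power is 63.5% by t-test on the effective number and 64.5% by normal approximation. A t-test on 22 participant means per group, with d = 0.5/√(46/91) = 0.703, gives 62.5%.

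So the 22 misses 90% on this more favourable reading as well.

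**6. Possible origin of the 22.** A one-sample formula, without the factor 2 for comparing two groups, gives (1.960 + 1.2816)²/0.25 = 42.03. Then 42.03 × 46/91 = 21.2, rounded up to 22, and 22 × 91 = 2002. This matches both printed numbers. An unstated halving of the variance for baseline adjustment would match them equally well, so the origin cannot be established from the article.

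**The case against.** The strongest reply is that nothing operational rests on the 22. Sections 2.2.2 and 2.2.3 both fix recruitment at 300, and both 300 enrolled and 240 evaluable exceed the 172 needed. This stands. A reader might infer from the failed arithmetic that the trial is underpowered; the documents do not support that, because the error in the 240 is on the safe side.

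Three other tempting readings also fail:

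- **That 91 days per woman conflicts with a six-month trial.** Section 2.4.1 names three months as a primary time point, and 91 days is about three months. The number of days hardly matters either: with 182 days the one-sample formula gives 42.03 × 91.5/182 = 21.1, which still rounds up to 22.
- **That the plan treats days as independent.** The sizing applies an ICC of 0.5 because days within a woman are correlated, and section 3 plans a within-subject analysis.
- **That the right number is 43 women per group.** The two-group day-level formula gives 84.06 × 46/91 = 42.5, so 43. But it needs the unstated day-level scaling of d and the back-calculated 91 days, and it reaches only 89.7% power by t-test on participant means. Printed beside 86, it would again leave the paragraph with two requirements for the same inputs.

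None of this reconciles 240 with 44 or makes either figure reproduce.

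**Conclusion.** The point holds as an internal contradiction and a failure to reproduce. For the stated inputs and a 1:1 comparison the requirement is 86 per group (172 in total). The stated 240 is 68 participants above that and corresponds to about 97% power, or to 90% power at d = 0.42. The stated 22 per group gives about 37% power with the participant as unit, or about 63 to 64% on the day-level reading.

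The participant-level results need only the stated d, alpha, power and allocation. The day-level result also needs d on the day-level standard deviation and 91 days per woman. An omitted factor 2 is a possible explanation of the 22 and no more than that.

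This should be fixed, but it does not threaten the trial: enrolment stays as it is, and the study is not underpowered for its stated effect.

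**What to change.** Keep 300 enrolled, and in section 2.2.3:

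1. Delete the sentence that gives 2002 days and 22 participants per group. Do not replace it with 43 per group.
2. Name the participant as the unit for sizing.
3. State that d = 0.5 at 90% power and two-sided 0.05 needs 86 per group (172 in total).
4. State that 150 per group with 20% dropout leaves 150 × 0.8 = 120 per group, which gives about 97% power at d = 0.5 and 90% power at d = 0.42.

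The cost is a correction to one paragraph. Recruitment and data collection are unaffected.

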#### 2.2.4. Randomization, Allocation and Blinding

After the first experimental visit (T0), the participants will be randomized using a computer-generated randomization list into one of the two conditions with a 1:1 allocation. The allocation will be transmitted using numbered (0 = control/1 = Intervention), opaque and sealed envelopes, which will be given to the young women and then registered by the data collectors. The assessors will be blinded to the treatment allocation, although double blinding is not applicable in interventions of this nature as it is impossible to conceal the allocation from the participants. The participants will be instructed not to reveal their allocation to the assessors to ensure unbiased assessment.

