**Figure 2 healthcare-11-01279-f002:**
[figure not shown]
Screenshots examples of the WISE application. (**A**) HIIT video sessions. (**B**) Sleeping tips. (**C**) Well-being tips. (**D**) The activity monitoring tool. (**E**) The weight and sleep monitoring tool.

**Table 1 healthcare-11-01279-t001:** Timeline for enrolment, interventions and assessments.

	Study Period							
	Selection Visit	T0	Intervention					
TIMEPOINT	M-_1_	0	M_1_	M_2_	M_3_/T1	M_4_	M_5_	M_6_/T2
ENROLMENT:								
Eligibility screen	X							
Informed consent	X							
Randomization		X						
INTERVENTIONS:								
Intervention group								
Control group								
ASSESSMENTS:								
Step count								
Adherence								
IPAQ		X			X			X
Height		X						
Weight		X			X			X
Body composition		X			X			X
Plank test		X			X			X
HLPCQ		X			X			X
PSQI		X			X			X
PACES		X			X			X
Period pain		X			X			X
CPM		X			X			X
6MWT		X			X			X

IPAQ, International Physical Activity Questionnaire; HLPCQ, Healthy Lifestyle and Personal Control Questionnaire; PSQI, Pittsburgh Sleep Quality Index; PACES, Physical Activity Enjoyment Scale; CPM, Conditioned Pain Modulation; 6MWT, 6 Minutes Walking Test. Continue line: duration over time.

**Table 2 healthcare-11-01279-t002:** BCT implementation in the intervention group following Michie et al.’s taxonomy [34].

BCT	Implementation in the WISE RCT
Goal setting behavior (1.1)	Set monthly step goal
Feedback on behavior (2.2)	Feedback on daily steps via the activity monitoring tool included in the application with weekly graphs
Self-monitoring of behavior (2.3)	Weekly diary used to document whether participants performed the exercise video and if they were engaged in any additional exercise during the study period
Feedback on outcome(s) of behavior (2.7)	Bioimpedance sheet with all the information of the changes in their body composition after 3 and 6 months of exercise
Social support (practical) (3.2)	Social days created so the participants can exercise together in real life
Social support (emotional) (3.3)	Promote social interaction through social media groups
Instruction on how to perform a behavior (4.1) Behavioral practice/rehearsal (8.1) Demonstration of the behavior (6.1)	Exercise videos
Information about health consequences (5.1)	Tips and information about the benefits of exercise and a healthy lifestyle given through the application
Prompts/cues (7.1)	Push notification through the application
Graded tasks (8.7)	Exercise program with increased difficulty

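### The envelopes are described as numbered only by arm code, and the assessor-blinding claim is not reconciled with registration of the allocation by the data collectors

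*Protocol article*

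**What the plan says.** All of the relevant text on allocation is in section 2.2.4 of the protocol article.

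- **Timing and source:** "After the first experimental visit (T0), the participants will be randomized using a computer-generated randomization list", with 1:1 allocation.
- **Carrier of the allocation:** "numbered (0 = control/1 = Intervention), opaque and sealed envelopes".
- **Handling:** "opaque and sealed envelopes, which will be given to the young women and then registered by the data collectors".
- **Blinding:** "The assessors will be blinded to the treatment allocation". Blinding of participants is acknowledged to be impossible.
- **Safeguard:** "The participants will be instructed not to reveal their allocation to the assessors to ensure unbiased assessment".

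Section 2.3.1 places all baseline measurements at T0, before the intervention starts, and says that the three experimental sessions are identical. Section 2.4.1 has daily steps, the primary outcome, recorded by the smartwatch. Table 5 describes the plank test: one departure from correct form is allowed, and the test stops at the second or if the participant fails to recover after the first warning.

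**The concern.** Two separate protections are involved.

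**Concealment.** A sealed opaque envelope works because nobody can tell its content before it is irrevocably assigned, and because a serial number fixes which envelope comes next. The numbering described here does neither job. An arm code that can be read from outside reveals the content, and a label that takes only two values does not order the envelopes. Since allocation follows T0, the person handing over the envelope may already know how the participant performed. Selective assignment at that moment would undo the randomization for the participants concerned.

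**Assessor blinding.** The data collectors learn the arm when they register it. If any of them later run T1 or T2, those visits are not blinded. What is at stake is the credibility of outcomes that depend on an observer's decision.

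**Working it through.** No arithmetic applies: the point depends on no sample size, power or error rate, and the document gives no figure to reproduce. The check sets the statements side by side.

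**Step 1: what the number on the envelope is.** In section 2.2.4, the word for numbering describes the envelopes, and the bracket directly after it defines the numbers as 0 for control and 1 for intervention. No other number is mentioned. There are two possible readings:

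| Reading | Can the arm be known before opening? | Does the text fix the order of use? |
|---|---|---|
| Code on the outside (literal) | Yes | No |
| Code on the slip inside | No, if properly sealed | No |

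Under the literal reading concealment fails. Under the other it may hold, but the article still describes nothing that ties a given envelope to the next place on the computer-generated list.

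**Step 2: what is known when the envelope is handed over.** Consent and eligibility are settled at the selection visit (section 2.3.1, Table 1). T0 is then completed, and randomization follows. A visible code therefore cannot influence who enters the trial or how T0 is measured. It could influence which arm a participant with known T0 results receives, if staff depart from the list.

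**Step 3: who knows the arm afterwards.** Section 2.2.4 gives data collectors the task of registering the allocation, and the next sentence says that assessors are blinded. The two terms are neither equated nor separated anywhere in the article.

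| Case | Is the blinding claim tenable? | Does the stated safeguard help? |
|---|---|---|
| Data collectors and assessors are different people, and assessors cannot see the record | Yes | Yes |
| Data collectors also run T1 or T2 | No | No, because they registered the arm themselves |

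**Step 4: which outcomes depend on the assessor.**

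- Daily steps are recorded by the device, so assessor knowledge has no direct route to the primary outcome.
- IPAQ, HLPCQ, PSQI, PACES and the period-pain scale are completed or rated by the participant.
- Body composition is read from an impedance analyzer, which also calculates BMI.
- The plank test is stopped when form is judged to have failed for the second time, or not to have been recovered after a warning. Here the article itself describes an observer's decision.
- The 6-minute walk is measured as distance. Table 5 describes no judgement or encouragement by staff.

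**The case against.** The strongest reply is that the section, read as a whole, favours sound practice. Describing the envelopes as opaque and sealed would be pointless with the arm printed on the outside, so the bracket may simply decode the slip inside. Asking participants not to disclose their arm makes sense only if assessors do not already hold it, which suggests two groups of staff. An article may also leave external labelling and custody of the list to the full protocol.

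Much of this stands. It rules out several stronger statements that a reader might infer:

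- **That the section contradicts itself.** This would require data collectors and assessors to be the same people, and the article uses two terms without linking them. The blinding claim is unreconciled, not disproved.
- **That concealment has certainly failed.** The code may be inside the envelope.
- **That the bioimpedance feedback unblinds assessors.** Table 2 lists "Bioimpedance sheet with all the information of the changes in their body composition after 3 and 6 months of exercise" among the techniques for the intervention group, but no text says that controls receive no such sheet. Table 4 does not list it as a difference between the groups, and nobody is named as handing it over.
- **That assessor knowledge would distort body composition or the 6-minute walk.** The document describes no such route.

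The reply does not remove the point. The article chose to describe the mechanism, and the only numbering it gives is the arm code. Its only stated protection for assessors works only if the roles are separate, which it does not say.

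**Conclusion.** The point holds as a mechanism that is badly fixed in its wording and a blinding claim that is not secured.

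- **Concealment:** followed literally, the description lets staff see the arm and choose an envelope after T0 results are known. This rests on the code being visible outside, and actual harm would further require staff to depart from the list. If that happened, the resulting imbalance would not be confined to assessor-run outcomes.
- **Blinding:** the claim fails if those who register the allocation also run T1 or T2, and can stand if they do not. The article does not settle which. The main exposure is the plank test, one secondary outcome; assessor knowledge does not act directly on device-recorded steps.

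The size of any bias cannot be derived from the document. The case for acting is that the correction is simple, while a failure of concealment could not be repaired in the analysis.

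**What to change.** In section 2.2.4:

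1. Describe sequentially numbered, opaque, sealed envelopes. The serial number on the outside should match the randomization list, the arm code should appear only inside, and the envelopes should be opened in order after T0 is complete.
2. State that whoever registers the allocation does not run the T1 or T2 assessments, and that assessors have no access to the record.
3. If existing staff cannot be separated in this way, withdraw the assessor-blinding claim for the staff-judged tests, the plank test first among them.

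**Cost:** the first item is relabelling and a sentence of text. The second is also only a sentence if the roles are already separate. If they are not, the registration task has to be reassigned, and the article gives no staffing information from which to judge that effort. The third item costs nothing beyond the wording. No change to sample size, visits or analysis is needed.
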